## Abstract

**Background:**

Keeping a certain level of physical activity has beneficial effects on the body itself but also, surprisingly, on cognition: specifically, physical high-intensity intermittent aerobic exercise (HIE) can show improvement on cognitive executive functions. Although, in some cases performing strength or aerobic training is problematic or not feasible. Immersive virtual reality (IVR) can induce the illusory feeling of ownership and agency over a moving virtual body, therefore showing comparable physiological reactions: for example, if an individual is sitting on a chair but his virtual body climbs a hill, the individual’s heart rate increases coherently, as if he is actually walking.

In this study, we investigate whether this same illusion can show beneficial consequences on the body as well as on executive functions (using the color-word matching Stroop task) and on its neural substrates (using functional near-infrared spectroscopy [fNIRS]).

**Methods:**

In a cross-over randomized controlled trial, 30 healthy young adults will experience HIE training in IVR (i.e. the virtual body will perform eight sets of 30 s of running followed by 30 s of slow walking, while the participant is completely still) according to two random-ordered conditions: during the experimental condition, the virtual body is displayed in first-person perspective (1PP), while in the control condition, the virtual body is displayed in third-person perspective (3PP). To confirm that individuals have the illusion of ownership and agency over the virtual body in 1PP (and not in 3PP), we will record the heart rate, in addition to subjective questionnaires. Before and after every IVR sessions (one week apart), we will measure cortical hemodynamic changes in the participants’ prefrontal cortex using the fNIRS device during the Stroop task’s execution.

**Discussion:**

From a theoretical perspective, we could prove that the sense of body ownership and agency can modulate physical and cognitive parameters, even in the absence of actual movements; from a clinical perspective, these results could be useful to train cognition and body simultaneously, in a completely safe environment.

**Trial registration:**

University Hospital Medical Information Network Clinical Trial Registry, UMIN000034255. Registered on 1 October 2018.

**Electronic supplementary material:**

The online version of this article (10.1186/s13063-019-3591-1) contains supplementary material, which is available to authorized users.

## Background

It is widely known that a constant level of physical exercise is one of the key components for overall health and to postpone aging-related disorders [1–5], in somatic and cognitive terms [6–10]. Surprisingly, several recent studies have shown that aerobic exercise has beneficial consequences not only on bodily but also on cognitive functions [11–16]. Intriguingly, Kujach et al. [17] demonstrated that a high-intensity intermittent exercise (HIE)-based intervention has beneficial immediate effects on the cognitive function of sedentary young adults similar to the benefits of long-term physical adaptations [15, 18]: specifically, the HIE model they proposed consists of eight sets of 30 s of cycling exercise at 60% of the individual’s maximal aerobic power followed by 30 s of rest, for a total of 8 min. Before and after the HIE, they repeated the color-word matching Stroop task (hereinafter, Stroop task) that is widely known to measure executive functions [19–21] and they recorded with a multi-channel functional near-infrared spectroscopy (fNIRS), which allows the monitoring of cortical hemodynamic changes, specifically in the prefrontal cortex (PFC), where executive functions are localized [22, 23]. Significant behavioral improvement in inhibiting cognitive conflict induced by the Stroop-interference effect occurred after HIE and, as a neural counterpart, they found a significant increase in the cortical activation in the left dorsolateral prefrontal cortex (DLPFC) specifically after the HIE session. Therefore, this HIE-based exercise intervention may provide a strategy for improving cognitive and cardiovascular functions at the same time.

Unfortunately, in some cases, it is complicated (e.g. sedentary, very busy people, elderly in a frailty condition), sometimes even impossible (e.g. cardiopathic individuals, patients recovering after long-term disease, patients with motor impairment), to perform constant physical exercise [24] or even a short-term high-impact physical exercise. These lifestyles characterized by the absence of constant physical activity clearly have negative effects on the wellbeing of the body and, as described previously, can limit the improvement of cognitive abilities or even contribute to their decline.

For those situations, a potential solution could be to bypass the actual execution of movements by creating a condition where bodily and cognitive reactions are comparable to real ones. In order to do so, an effective innovative technique seems to be immersive virtual reality (IVR) because it allows showing a virtual world and, more importantly, a virtual body (also called avatar) that is extremely realistic and plausible [25–28]. With the sole use of a visor equipped with two that show the virtual environment [29], it creates a strong feeling of “being there,” just exploiting the visual stimulation [30–37] (different from what happens with other multisensory illusions; see for example [27–29]).

Several recent papers have shown that it is not only the simple display of an avatar in first-person perspective (1PP) that creates the illusory sense of body ownership (SoBO) over the virtual body [38–40], but its movements also create the illusory sense of agency (SoA) over them [32, 33, 41]; the actions performed by their own virtual body are subjectively considered as own generated and they arise subjective, behavioral, and physiological reactions in the real individual’s body perfectly analogously with what happens in the physical world [32, 33]. For example, when the movements of their own virtual body do not match the real ones, an unconscious adjustment of the actual performance occurs, driven by the sense of body ownership over the avatar [41]. But even in the absence of actual movements, if the virtual body moves while the real body is totally still, the illusion can trigger measurable reactions perfectly comparable to the ones during an actual movement execution, online [33, 41] or in terms of consequences [32, 42, 43]: interestingly, for our purposes, it has been shown that if the virtual body, displayed in 1PP, climbs a hill, the real participant’s heart rate (HR) increases, exactly as would happen in the physical world. In this case, it seems to be a physiological counterpart of the SoBO visual illusion [33]. In summary, IVR can provide effective investigating methods to better understand the relationship between SoBo and SoA [44] and can provide potential solutions, complementary to the existing ones, for a clinical population (see [43] for a review).

### Purpose

In this study, we combined the efficacy of the HIE on cognitive functions [17] with the possibility of manipulating SoBO and SoA offered by IVR [33, 41]. Our goal is to demonstrate whether a virtual HIE-based intervention performed exclusively by the considered-as-own virtual body, while the real individuals’ body is totally still (hereinafter vHIE), has acute cognitive and somatic beneficial effects on the real body, comparable to the ones that arise after actual physical training. We will compare the behavioral performance (speed and accuracy) with the Stroop task during the recording of the brain activity of the PFC with fNIRS (as in [15]), before and after the vHIE, in two interventions where we manipulate the visual perspective (1PP vs 3PP), known to induce or disrupt the SoBO and SoA over the avatar.

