### Measurements

#### Heart rate

During the interventions, in order to check if participants actually perceive the virtual body as their own (in 1PP and not in 3PP), we will record the HR with a Polar H10 HR monitor, controlled by a specific application via Bluetooth. Participants have to wear an elastic strip around the chest on which the HR monitor is attached, positioning it close to the heart, in order to record the HR for each intervention conditions (1PP and 3PP) during the baseline (4 min), the intervention (4 min running, 4 min slow walking, for a total of 8 min) plus an extra 30 s (where the participant is still with closed eyes) to check for eventual delay in the recording and to wait for the synchronization of the HR.

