### Outcomes

#### Primary outcomes

Considering that the main goal of this study is to determine that vHIE intervention performed with the own virtual body (1PP) has a beneficial effect on cognitive executive functions, the primary outcome of this study is the Stroop task (i.e. the cognitive domain), specifically the two related measurements (RT primarily and ER secondarily). The Stroop task is considered the primary outcome here because it is widely known as a measure for executive brain functions [21, 55]. As a key effect of the Stroop task, we will consider the so-called “Stroop interference” as the (average of incongruent trials– average of neutral trials) contrast, which is assumed to represent Stroop interference, for both RT and ER in each condition (1PP and 3PP).

Specific timepoints (before and after the vHIE) will be considered, but the main comparison in order to find a significant effect of vHIE on cognitive functions will be 1PP versus 3PP.

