## Discussion

The background of this RCT protocol study starts with two assumptions, based on data presented in the literature: (1) HIE has acute beneficial consequences on executive functions and their neural basis [17, 67]; and (2) the movements of their own virtual body can generate measurable consequences on their real body, comparable to the ones when we actually move [33, 41].

Consequently, we hypothesized that the same HIE intervention performed by their own virtual body (and not by the real participants’ bodies) can have the same beneficial acute effects on executive functions.

In order to confirm our hypothesis, 30 healthy young adults will undergo a vHIE, where the virtual body exclusively (the real body is still sitting) will perform 8 min of training, alternating 30 s of running and 30 s of slow walking; the same vHIE will be performed in two intervention conditions: 1PP, the virtual body will be displayed with the real one, spatially replacing it, and so it will be considered as their own; in 3PP, the virtual body will be displayed 1.5 m away on the right side of the real one, and so it will simply be considered as someone else. During the vHIE, we will record the HR: we predict finding a fluctuating trend of the HR during the intervention in 1PP (and not in 3PP), coherent with the virtual movements, as if the individual is actually performing them. In addition, we will ask the participants to report verbally any subjective feelings during the intervention, predicting that increased sensations of SoBO and SoA in 1PP respect to 3PP will be found.

To test our main hypothesis about acute beneficial effects on executive functions, before and after the two vHIE intervention conditions, we will record the participants’ performance of the Stroop task; at the same time, we will record cortical hemodynamic changes over the PFC with the fNIRS. We predict finding better performance, in terms of reaction time and accuracy, in the Stroop task and higher activation of the neural correlated areas (i.e. PFC) after the vHIE in 1PP (and not after 3PP).

If we confirm our hypothesis, it means that virtual training performed only with the own virtual body can raise the same physical but especially cognitive and neural consequences of a “real” physical one.

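### The objective and planned conclusion promise a bodily benefit, but no listed outcome can establish one: heart rate is analysed only during viewing and read as evidence of embodiment

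*Protocol article*

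**What the plan says.** **Objective.** Purpose states the goal as showing whether the virtual intervention "has acute cognitive and somatic beneficial effects on the real body", on a par with those that follow real exercise. The abstract's Background paragraph asks whether the illusion "can show beneficial consequences on the body as well as on executive functions".

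**Comparison.** Straight after the goal, Purpose names what will be compared: "We will compare the behavioral performance (speed and accuracy) with the Stroop task during the recording of the brain activity of the PFC with fNIRS". No bodily measure appears there.

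**Outcomes.** Under Primary outcomes, "the primary outcome of this study is the Stroop task (i.e. the cognitive domain"), with response time first and error rate second. Secondary outcomes are the fNIRS oxygenated-haemoglobin data, described as the neural side of the behavioural results. Additional outcomes are heart rate, the online and offline questionnaires, and the mood scale (TDMS).

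**Role of heart rate.** The Heart rate section under Measurements says it is recorded "in order to check if participants actually perceive the virtual body as their own". Statistical analysis places it in a first phase that checks whether the intervention worked, and gives the hypothesis test to a second phase made up of Stroop and fNIRS. Heart rate data interprets a first-person (1PP) increase as the physiological side of embodiment.

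**Planned conclusion.** The Discussion says that confirming the hypothesis would mean virtual training "can raise the same physical but especially cognitive and neural consequences" of real physical training.

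**The concern.** An objective that claims benefit needs an outcome that can show benefit. Here the objective has a cognitive and a somatic part. The cognitive part has an instrument, a contrast and a test. The somatic part has none: the only bodily measure has another job, and nothing in the document defines a change in heart rate as beneficial. A brief rise in a seated viewer shows that the body responded, not that it gained anything.

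The sentence in the Discussion makes this matter. It ties a conclusion about physical consequences to confirmation of a hypothesis that is tested without physical data. The same section goes on to applications in sedentary people, people with heart disease and patients with motor disorders, and speaks of benefits equal to those of physical training. A reader from those fields could take a positive Stroop result as support for a bodily effect that the trial did not assess.

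**Working it through.** The document gives no figure on this point to reproduce. The stated sample size of 28 (30 recruited) rests on Stroop response time and does not bear on it. The check sets the objective against the outcomes and then looks at what the heart-rate ANOVA can show.

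**Step 1. Count the measures** (Outcomes, Measurements, Statistical analysis).

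| Measure | Domain | Compared before vs after the intervention | In the hypothesis-testing phase |
|---|---|---|---|
| Stroop response time | cognitive | yes | yes |
| Stroop error rate | cognitive | yes | yes |
| fNIRS oxygenated haemoglobin | neural | yes | yes |
| Heart rate | bodily | no | no |
| Online questionnaire | subjective ownership and agency | no | no |
| Offline questionnaire | subjective ownership, agency, effort | no | no |
| TDMS | mood | yes | no (only related to the Stroop data under Correlations) |

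- Bodily measures outside the brain: 1 of 7.
- Bodily measures compared before and after the intervention: 0 of 7.
- Bodily measures in the hypothesis-testing phase: 0.

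The offline item on physical effort and the TDMS arousal score are self-reports of feeling, not measures of bodily benefit.

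**Step 2. When heart rate is used.** It is recorded for 4 min of baseline, 8 min of intervention (4 min running + 4 min walking) and an extra 30 s. Heart rate data averages three periods of 4 min: baseline (HRb), running (HRr) and walking (HRw). The extra 30 s is meant for recording delay and synchronisation and enters neither formula. So the analysed heart rate is a during-viewing quantity, whereas the benchmark in Purpose is the effects that arise after real training.

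**Step 3. What the ANOVA tests.** The plan defines dHRr = HRr − HRb and dHRw = HRw − HRb, and runs a 2 × 2 ANOVA of speed by condition. Using 1 for first person and 3 for third person (3PP), the effects are:

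- speed: (dHRr₁ + dHRr₃)/2 − (dHRw₁ + dHRw₃)/2
- condition: (dHRr₁ + dHRw₁)/2 − (dHRr₃ + dHRw₃)/2
- interaction: (dHRr₁ − dHRw₁) − (dHRr₃ − dHRw₃)

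Add any constant c to all four cells. In each effect c appears once with a plus and once with a minus sign (c − c = 0), so all three are unchanged. The same is true of a pairwise comparison of dHRr₁ with any other cell. These tests therefore show whether running in first person stands above the other cells, but not whether mean dHRr₁ exceeds zero, that is, whether heart rate rose above its own baseline. The latter needs the mean of dHRr₁ with its own interval.

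**Step 4. Put the chain together.** The hypothesis is confirmed by Stroop and fNIRS. The Discussion derives physical consequences from that confirmation. The one bodily measure is spent on a prior question, whether the avatar was embodied. No step leads from the data to somatic benefit.

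**The case against.** The strongest reply is that the inferential parts of the article are about cognition. Primary outcomes, Statistical analysis and Stroop task's RT and ER all name executive function or cognition as the main target, and Sample size rests on Stroop response time. This stands. A reader might infer that a large share of the trial's question is unanswerable. The documents do not support that: the declared main goal can be answered as planned.

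Second, heart rate is a listed additional outcome, and elsewhere the article speaks of bodily reactions or of modulating physical parameters. Heart rate during viewing can address that weaker statement. This also stands, but it does not reach the word beneficial, which Purpose and the abstract both use.

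Third, a reader might infer that a successful embodiment check will be presented a second time as an efficacy result. No analysis section plans this: heart rate sits in the first phase and is read as embodiment only. The Discussion sentence is conditional and speaks of consequences rather than benefits. The problem lies in the wording of objective and conclusion, not in a planned misuse of the heart-rate test.

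Fourth, the heart-rate statement is a prediction, not a decision rule, and cell means with intervals may be in a fuller plan. That is fair, so the interval is offered as an inexpensive safeguard and not as the correction of an error.

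That an article condenses a fuller protocol does not remove the main point. This one lists its outcomes and states the purpose of heart rate, and the mismatch lies within that text.

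**Conclusion.** The point holds in a limited form. Purpose and the abstract promise a benefit to the body, and the Discussion would draw a physical conclusion from a hypothesis tested only with cognitive and neural data. None of the seven listed measures can establish a bodily benefit. The single bodily one is analysed during viewing and interpreted as embodiment.

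The effect is on what the trial may conclude. The two-session cross-over design, the primary Stroop comparison and the sample size are untouched. The conclusion assumes that fNIRS is taken as the article takes it, as the neural counterpart of cognition, and that a transient heart-rate change during viewing is a response and not in itself a benefit. The document offers no argument to the contrary. The remark on the ANOVA is algebraic and needs no assumed heart-rate values.

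**What to change.** 1. In Purpose and in the abstract's Background, limit the benefit objective to executive function and its cortical correlates.
2. In the Discussion, limit what confirmation of the hypothesis would mean to the same two domains, and remove the claim of equal physical consequences.
3. Keep heart rate as an additional outcome, but describe it as an acute physiological response and embodiment check, and state that it is not evidence of somatic benefit.
4. Under Heart rate data, add that mean dHRr in 1PP will be reported with its confidence interval against zero, alongside the comparisons between cells, before an increase in heart rate is claimed.

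The cost is a narrower claim, some rewording and one extra interval from data already being collected. No new measurement, participant or visit is needed.

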## Methods/design

The protocol was developed according to the SPIRIT (see Additional file 1) and CONSORT (see Additional file 2) guidelines for randomized controlled trials (RCT) [45]. The schedule for this study is displayed in Fig. 1, while the general procedure is shown in Fig. 2.

**Fig. 1 Fig1:**
[figure not shown]
Schedule of enrolment, interventions, and measurements, according to SPIRIT guidelines

**Fig. 2 Fig2:**
[figure not shown]
General procedure of the study. **a** The protocol of one experimental session (in both sessions the procedure is the same, the intervention condition changes) with its timeline. The first part describes the measurements before the intervention (TDMS and Stroop task with fNIRS recording); the central part corresponds to the vHIE intervention (that, according to the session, may be in 1PP or 3PP). **b** The intervention details: every 30 s, the speed of the avatar changes from slow walking to running; at specific timepoints, we will administer the online questionnaire for SoBO and SoA. The third part of A. describes the measurements after the intervention (same as before the intervention)

### Trial design

This study is a cross-over (within-subjects) RCT conducted at the Smart-Aging Research Center (Institute of Development, Aging and Cancer, Tohoku University), Sendai City, Miyagi Prefecture, Japan. All participants will perform both experimental and control conditions (in other words, all participants will act as their own controls). This study (version 1.0) was registered with the University Hospital Medical Information Network (UMIN) Clinical Trial Registry (UMIN000034255) on 1 October 2018.

### Participants recruitment and eligibility criteria

Thirty healthy young adults (15 women) will be recruited among students of Tohoku University (Sendai, Japan) via a specific online system. They will be reimbursed 1000 Japanese Yen per hour for their participation.

Participants must be native Japanese-speaking men and women aged 20–35 years and self-report to be right-handed. In addition, they have to report no history of neurological, psychiatric, or motor disorders and normal color vision. To avoid eventual problems during the IVR sessions, we will exclude individuals that report to be extremely sensitive to motion sickness (e.g. nausea while driving a car).

### Randomization of interventions

The two intervention conditions will be administered to all participants in two separate sessions (one week apart). Random assignment to the first intervention using an online program (http://www.graphpad.com/quickcalcs/index.cfm) will take place [43]. Each participant is first assigned to a condition non-randomly (the random number generator is seeded with the time and the day). The assignment of each individual is then swapped twice (to make sure it is really random) with the condition assignment of a randomly chosen participant. Half of the participants (15 individuals) will perform the experimental condition first, while the other half will perform the control condition first. The sequence, and with it the assignment to the first intervention condition, is hidden from the researcher that enrolls the participants until the intervention starts to avoid biases; once the intervention begins, the sequence is no longer blinded from anyone.

